#### Statistical analysis

The data analysis will use the intention-to-treat principle (where all available data, including records showing non-adherence to the protocol, from participants will be included in the analysis). Thus, imputation will not be used for missing data.

We will compare the proportions of the outcome measures using a chi-squared test and present results with a 95% confidence interval.

We will present Kaplan-Meier survival curves for analysis of hospitalizations, emergency department visits, entry into aged residential care, and mortality within subgroups. Subgroups will include control low frailty, control medium frailty, control high frailty, intervention low frailty, intervention medium frailty, and intervention high frailty. The analyses will be controlled for age and sex, with death as a censored event. We will then conduct a competing risk analysis using cumulative incidence functions (CIF). For example, where entry to aged residential care is the primary event of interest, death is the competing event. The CIFs are the probability of observing these events before the end of the 6-month follow-up period.

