### Participants

Participants will be eligible for inclusion if they are as follows:
Are aged ≥65 yearsHave undergone an interRAI Home Care [24] or contact [25] assessmentAre regularly taking at least one anticholinergic or sedative medication as shown in the interRAI or dispensing records.

Participants will be excluded from the study for any of the following reasons:
Not consenting for their interRAI data to be used for researchHaving a psychiatric disorder or dementia disease (e.g., Alzheimer’s disease, dementia, schizophrenia, abnormal thought processes, delusions, hallucinations)Scoring 3 or higher on the interRAI Cognitive Performance ScaleHaving a terminal illness with life expectancy ≤6 monthsDetermined as non-frail by having no deficits in the frailty indexHaving an initial DBI score of <0.5 (DBI score of 0.5 is the equivalent of one DBI medication being taken at the minimum efficacious dose) [14].Having a potentially life-threatening drug interaction requiring urgent medical intervention (during the study period)

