#### Clinical responsibility

Clinical responsibility for all participants remains with their primary care GP. Participants will be asked to contact their GP if they feel unwell during drug withdrawal. If disease relapse occurs or unwanted adverse drug effects occur, the medicine will be re-prescribed as seen appropriate by a participant’s GP.

Reasons for withdrawal or dropout, other than death, will not be recorded in the study. However, the research team will access and analyze hospital admissions. In addition, any notification of incidents received from participants or their GPs will be passed onto an internal data monitoring committee for review (data monitoring and safety are explained in the latter part of the document).

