### Outcomes

In this study, five outcome scenarios are possible: (1) completion of the trial, (2) entry into aged residential care (ARC) before completion (this would be linked to a change in GP and medication control), (3) prolonged hospitalisation, (4) death, and (5) withdrawal or other loss to follow-up. The first two outcome scenarios would involve the post medication review being undertaken either with the participant or via the medical records of a care facility. The third outcome scenario could lead to delays in recording the post-intervention review or may lead to any of the four other scenarios.

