#### Primary outcome

The primary outcome will be the change in a participant’s DBI (ΔDBI) between the time of the baseline interRAI assessment (T1) and the time of 6 months of follow-up (T2; ΔDBI = DBI_T1_ – DBI_T2_). Data for the calculation will be collected by comparing medication use pre-and post-intervention. We will determine if there is a greater reduction in the DBI of participants in the experimental arm of the trial compared with participants with the same level of frailty in the control arm. Subgroup analysis will determine if deprescribing is more pronounced for those with more severe frailty.

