### Statistics methods

#### Power and sample size

For this RCT, we define the clinically significant change in DBI as 0.5, the equivalent of one medication contributing to DBI given at the minimal efficacious dose [14]. Approximately 4% of recent interRAI assessments show a ΔDBI ≥ 0.5 over 6 months. Therefore, a meaningful outcome from deprescribing in this study would be to increase the percentage, in the intervention cohort, with a DBI change ≥of 0.5 by 10% points. This would bring the percentage ΔDBI ≥ 0.5 over a 6-month period to 14%.

The null hypothesis is that there is no difference in proportions with a ΔDBI of ≥ 0.5 over 6 months between the control and intervention groups, given that 4% of participants in the control group have a ΔDBI of ≥0.5. Therefore, to disprove the null hypothesis, we need to detect a change in the number of participants of 10% or more with a ΔDBI of ≥0.5 with a power of 90% at an *α*=0.05. This requires 167 participants in each arm of the study, 334 in total.

For each frailty stratum under the null hypothesis, there will be no difference in change in DBI between the control and intervention groups and assume 4% of participants in the control group have a reduction in DBI of ≥0.5, then to detect a change in the number of participants of 20% or more with a reduction in DBI of ≥0.5 with a power of 80%, and at *α*=0.017 (0.05/3), requires 56 participants in each arm of the study (112 in each stratum, 336 in all).

It is estimated that over 12 months within the target areas of the district health boards’ approximately 650 participants will meet the basic inclusion criteria, including the minimum DBI. In addition, previous data suggest that approximately 50% of the study’s cohort will take the target medicines, and therefore, 325 people would be eligible to take part in the study per annum.

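### The primary responder test is a complete-case analysis under an intention-to-treat label, and 167 per arm is a count of evaluable participants with no margin for loss

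*Protocol article*

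**What the plan says.** The Statistical analysis section states: "The data analysis will use the intention-to-treat principle (where all available data, including records showing non-adherence to the protocol, from participants will be included". The next sentence draws a consequence: "Thus, imputation will not be used for missing data". The test follows: "We will compare the proportions of the outcome measures using a chi-squared test and present results with a 95% confidence interval".

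Under Primary outcome, the change in DBI is the baseline value minus the 6-month value, and "Data for the calculation will be collected by comparing medication use pre-and post-intervention". Table 3 and the Power and sample size section turn this into the proportion with a reduction of at least 0.5.

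The Outcomes section lists five ways in which participation can end. It describes a follow-up medication review for two of them: completion, and entry into aged residential care (through the facility's records). Prolonged hospitalisation may delay the review or lead to another scenario. No review is described for death or for "5) withdrawal or other loss to follow-up".

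The Clinical responsibility section adds: "Reasons for withdrawal or dropout, other than death, will not be recorded in the study". The exclusion list under Participants includes a dangerous drug interaction "requiring urgent medical intervention (during the study period)". On size, the article says: "This requires 167 participants in each arm of the study, 334 in total". It gives no attrition rate.

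**The concern.** Intention-to-treat has two parts: people are analysed in the arm to which they were allocated whatever they then did, and everyone randomised stays in the comparison. The article's definition secures the first part by keeping non-adherent records. It does not secure the second, because using all available data leaves out anyone whose outcome is not available. Nor does a ban on imputation follow from either part.

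This is a stated rule, not a detail left to a statistical analysis plan. A later plan could repair it only by departing from the rule or by defining an outcome for people without a 6-month value.

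Two things are at stake. First, if loss differs between arms or depends on whether the DBI would have fallen, the responder proportions among those reviewed are not those of the randomised groups, and recruiting more people does not cure that. Second, the sample size gives the stated power only if nobody is lost, although the article itself foresees death and loss to follow-up in a frail population aged 65 or over.

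**Working it through.** **Who has no endpoint value.** The change in DBI is undefined without a 6-month value.

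- Completers and aged-residential-care entrants are reviewed.
- Hospitalised participants may only be late.
- A telephone review was approved for COVID-19 lockdown (Ethics and protocol changes).
- This leaves deaths, withdrawals and other losses. With no imputation, they are in neither numerator nor denominator.

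**Reproducing 167.** Inputs from Power and sample size: 4% against 14%, α = 0.05, power 90%; 1:1 allocation from Study design. Sidedness is not stated; two-sided is assumed because it reproduces the figure. With unpooled variance:

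n = (1.960 + 1.282)² × (0.04×0.96 + 0.14×0.86) / 0.10² = 10.507 × 0.1588 / 0.01 = 166.86, so 167 per arm.

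The match is exact, so there is no attrition margin. The pooled formula gives 171. The 336 quoted for the three frailty strata adds only two people.

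**Power after loss.** The article gives no attrition rate, so d = 10, 15 and 20% are assumptions, applied to 334 enrolled. Unpooled power is Φ(0.10 / √(0.1588/m) − 1.960), with m = 167(1 − d):

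| Loss d | Evaluable per arm | Power, unpooled | Power, pooled | Enrolment to keep 167 evaluable per arm, 167/(1 − d) |
|---|---|---|---|---|
| 0% | 167 | 90% | 89.5% | 167 (334 in all) |
| 10% | 150 | 87% | 86.1% | 186 (372) |
| 15% | 142 | 85% | 84.1% | 197 (394) |
| 20% | 134 | 83% | 81.9% | 209 (418) |

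Counting missing as non-response multiplies both rates by (1 − d) if loss is unrelated to response. With all 167 per arm kept, pooled power is 85.7, 83.5 and 81.0% at the same three rates. Keeping everyone in this way therefore costs about one percentage point or less against complete cases.

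**Possible bias.** Suppose the true rates among all randomised are 14% and 4% (10 points), and 15% of an arm is lost, all of them non-responders. Responders are unchanged and the denominator shrinks to 0.85:

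- Loss in the intervention arm only: 0.14/0.85 = 16.5%, and 16.5 − 4.0 = 12.5 points.
- Equal loss in both arms: 0.14/0.85 − 0.04/0.85 = 0.10/0.85 = 11.8 points.
- Loss in the control arm only: 0.04/0.85 = 4.7%, and 14.0 − 4.7 = 9.3 points.

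The third case shows that the error can also run against the intervention. If those lost in each arm would have responded at the same rate as those who stay, there is no bias.

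**The case against.** The strongest defence is that missing follow-up may be limited. Care-home entrants are reviewed, the review may take place at any time from 6 months on, and telephone contact was approved for lockdown. Someone who relapses and is re-prescribed a medicine need not leave the trial and can still be reviewed and counted as a non-responder. Overall power stays above 80% even at 20% loss. All of this stands, and it bounds the problem. It does not supply an outcome for deaths and withdrawals or make the inference valid.

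Five stronger readings are tempting and are not supported:

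- **That loss inflates the effect.** A reader might infer that people leave mainly from the intervention arm, having failed to sustain a reduction. Nothing in the article establishes this, and the 12.5-point figure is a constructed worst case.
- **That a post-randomisation exclusion is allowed.** The drug-interaction criterion has a time window that could run past allocation, but no section removes such people from the analysis, and non-adherent records are expressly kept. The envelope-return rule applies before the envelope is opened. The wording is an ambiguity to close.
- **That missingness cannot be examined, or that participant flow cannot be reported.** Reasons will not be recorded, which is a loss, but it is not a prohibition. The five scenarios can be counted by arm, and missingness can be compared with baseline DBI, frailty, admissions, mortality and dispensing, all of which are held or linked.
- **That the stated power is certainly not delivered.** Every attrition rate here is assumed. The article says what the comparison requires, not that enrolment stops at 334, and an allowance may sit in the full protocol.
- **That attrition explains the whole shortfall within frailty strata.** At 56 per arm, 4% against 24% and α = 0.05/3, unpooled power is already 78.6% with no loss, so part of any gap from 80% is choice of formula.

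**Conclusion.** The point holds in this form: the article attaches an intention-to-treat label to an analysis that, for the primary responder test, uses only participants with a 6-month review. That is certain from the text. Whether it biases the result, and in which direction, is not known from the document.

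On assumed 15% loss made up entirely of non-responders, a true 10-point effect would be reported as about 12.5 points (intervention arm only), 11.8 (both arms equally) or 9.3 (control arm only). That 167 per arm contains no attrition allowance is confirmed by exact reproduction, given a two-sided unpooled formula. The power cost is moderate: about 87, 85 and 83% at an assumed 10, 15 and 20% loss from 334 enrolled. The possible bias matters more than the lost power.

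**What to change.** - Delete the sentence that derives no imputation from intention-to-treat. Either describe the primary analysis as complete-case, or keep all randomised participants under a pre-stated rule for deaths and for missing 6-month values. Counting deaths as non-response is one choice among several; the plan should name its choice.
- Before unblinding, add three sensitivity analyses: multiple imputation using arm, baseline DBI and frailty stratum; missing counted as non-response; and a 6-month DBI derived from the linked PHARMAC dispensing records. The last measures what was dispensed, not what was in use at home, and applies only where linkage is available. The article does not say whether linkage continues after withdrawal.
- State that anyone who meets the drug-interaction criterion after allocation stays in the analysis set.
- State that 167 per arm is the number of evaluable participants, and give power over an assumed range of loss. If recruitment has closed, power can only be restated.
- Record reasons for leaving, when offered, from now on. Reasons for people who have already left may not be recoverable.

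The cost is revised wording, one data field, a slightly lower stated power and some extra analysis, most of it in deriving DBI from dispensing data.

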Lorazepam	N05BA06	Zolpidem	N05CF02
Lormetazepam	N05CD06	Zuclopenthixol	N05AF05
Methadone	N07BC02		

After enrolment, participants will be stratified using a frailty index (FI), which will be based on a cumulative deficit model using 15 relevant items common to the interRAI Homecare and Contact assessments. Cut-off values for each stratum will create three equal-sized frailty strata based on New Zealand interRAI HC and CA data used for developing the frailty index. Participants will be stratified into one of three frailty strata (low, medium, high) and allocated in a 1:1 ratio within each strata to the intervention and control arms of the trial.

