#### Randomization and allocation

Predefined randomization lists with a 1:1 allocation will be calculated by the study’s data manager using a Mersenne Twister algorithm. The algorithm will be repeatedly run until a list is identified that shows a difference in the total number of intervention and control arm participants of not more than three participants at any given point in the process. Centralized allocation is considered neither viable nor required in this community-based study setting, as the participants become available at random through the interRAI assessment process. The randomization list is securely stored on the university’s computer system and not available to any other research team member. Each frailty strata will have its randomization list and set of treatment allocations concealed in sequentially numbered sealed opaque envelopes. Allocations will be made by the study administrator, who will select the next allocation matching a participant’s frailty strata when the participant’s home visit is booked. The envelopes are opened after completion of the pre-intervention medication review. If a participant is discovered to be ineligible during the pre-intervention medication review, the corresponding envelope is returned and used with the next available participant.

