#### Secondary outcomes

Secondary outcomes measures will be compared between the two arms of the trial after 6 months and are outlined in Table 3. From the funder’s perspective, these include the number of hospitalizations, emergency department visits, entry into aged residential care, all-cause mortality, and cost-utility. In addition, we will measure the number of emergency department visits and unplanned hospital admissions. Data on entry into or change in the level of care in aged residential care will be extracted from relevant national databases by the analytical services of the Ministry of Health. Patient mortality data will be matched using participants’ National Health Index (NHI) number, added to the dataset, and analyzed using competing risk regression. In a separate analysis, we will conduct a health cost utility assessment.

**Table 3 Tab3:** Outcome measures and analysis

Outcome	Measure	Alternative hypothesis	Analysis
Drug burden change	Proportion ΔDBI ≥ 0.5	Intervention greater	*χ*^2^ comparison of proportions
Emergency department visits	Proportion	Remain the same or decrease	*χ*^2^ comparison of proportions
Unplanned hospital admissions	Proportion	Remain the same or decrease	*χ*^2^ comparison of proportions
Admissions into aged residential care	HR	Remain the same or decrease	CRRA
Mortality	HR	Remain the same or decrease	CRRA

*ΔDBI* change in Drug Burden Index, *WSR* Wilcoxon signed-rank test, *CRRA* competing risk regression analyses, *χ*^2^ chi-square

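### The overall DBI comparison is stated as an unstratified chi-square: it leaves out the frailty strata used in the randomisation and baseline DBI; the loss is small and the remedy nearly free

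*Protocol article*

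**What the plan says.** All places are in the protocol article.

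- **Design.** Study design: "Participants will be stratified into one of three frailty strata (low, medium, high) and allocated in a 1:1 ratio within each strata". Randomization and allocation adds: "Each frailty strata will have its randomization list and set of treatment allocations concealed in sequentially numbered sealed opaque envelopes".
- **Comparison described.** Under Primary outcome, the reduction in the experimental arm is to be "compared with participants with the same level of frailty in the control arm". The next sentence reads: "Subgroup analysis will determine if deprescribing is more pronounced for those with more severe frailty".
- **Test named.** In Table 3 (Secondary outcomes) the drug burden measure is "Proportion ΔDBI ≥ 0.5", analysed by a chi-square comparison of proportions. The same test is listed for emergency department visits and unplanned admissions. Statistical analysis repeats it: "We will compare the proportions of the outcome measures using a chi-squared test and present results with a 95% confidence interval".
- **Hypothesis and size.** Power and sample size states the overall null hypothesis for the two whole arms (4% v 14%, 90% power, α = 0.05, 167 per arm). It then sizes a comparison within each frailty stratum (4% v a 20-point increase, 80% power, α = 0.017, 56 per arm).
- **Covariates.** The only adjustment mentioned is in the time-to-event paragraph: "The analyses will be controlled for age and sex, with death as a censored event".
- **Baseline DBI.** Under Participants, an initial DBI below 0.5 is an exclusion.

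**The concern.** When allocation is stratified, the usual practice is to carry the strata into the analysis. If frailty predicts response, a test that pools over strata uses a standard error that is too large, because it counts between-stratum variation that the design has already balanced. The protocol's own hypothesis is that the reduction is larger in frailer people, so frailty is expected to bear on the outcome. The overall test as named also does not make the same-frailty comparison described under Primary outcome.

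Baseline DBI matters for a structural reason. Response is a fall of at least 0.5 and entry requires at least 0.5. Someone entering at 0.5 responds only by losing all DBI exposure, whereas someone entering at, say, 2.0 can reach the threshold in several ways. Both variables are determined before the allocation envelope is opened, so both are legitimate covariates.

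At stake are some precision in the main result and agreement between design, stated comparison and test.

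**Working it through.** **1. The plan's own figures.** The unpooled two-proportion formula, two-sided α = 0.05 and 90% power, gives

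n = (1.960 + 1.282)² × (0.04×0.96 + 0.14×0.86) / 0.10² = 166.9, so 167 per arm.

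This is the stated figure (the pooled-variance version gives 171). For a stratum, 4% v 24% at α = 0.05/3 and 80% power gives 57.8, so 58 against the stated 56. Both stated sizes are therefore those of plain two-proportion comparisons, one over the whole arms and one within a stratum. Neither formula contains a stratified or adjusted overall comparison.

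**2. How much the strata matter for the variance.** With equal strata and equal allocation, the unstratified test uses p̄(1−p̄). The stratified test uses the average of p_s(1−p_s). The gap is the between-stratum variance of the rates.

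- Assumed null rates 1%, 3%, 8% (mean 4%): p̄(1−p̄) = 0.0384. Between-stratum variance = (0.03² + 0.01² + 0.04²)/3 = 0.00087. Within = 0.0375. The standard error is inflated by √(0.0384/0.0375), about 1%.
- Assumed null rates 10%, 30%, 60% (mean 33%): 0.222 against 0.222 − 0.042 = 0.180. Inflation is √(0.222/0.180) = 1.11.

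The effect is thus small at the planned rates and grows only when events are common and differ widely by stratum.

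**3. Simulation, three strata of 56 per arm.** The documents give no stratum-specific rates, so these are assumptions chosen to average 4% and 14% (200,000 simulated trials each). CMH is the Cochran-Mantel-Haenszel test stratified by frailty.

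| Frailty effect | Control / intervention rates (%) | Power, plain v CMH | Type I error, plain v CMH |
|---|---|---|---|
| None | 4,4,4 / 14,14,14 | 91.5 v 91.4 | 4.8 v 4.8 |
| Moderate | 2,4,6 / 8,14,20 | 91.8 v 91.8 | 4.8 v 4.9 |
| Strong | 1,3,8 / 4,12,26 | 92.2 v 92.7 | 4.6 v 4.9 |

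Both tests fall slightly below 5% even when frailty has no effect, so part of the shortfall is not due to ignoring the strata. At null rates of 5, 15, 40% and 10, 30, 60% (means 20% and 33%), the plain test's type I error falls to 3.6% and 3.0%, while CMH stays at 5.0%.

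**4. Adding baseline DBI.** Each frailty stratum was split by an assumed low/high baseline DBI, 50:50 (100,000 trials). Power for the plain test, CMH by frailty, and CMH by frailty and baseline DBI was 91.7, 91.8 and 92.1% (moderate), and 92.2, 92.6 and 93.7% (strong). The gain over the plain test is about 0.4 to 1.6 points.

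**5. Events available for a model.** Expected responders are 167×0.04 + 167×0.14 = 6.7 + 23.4, about 30. Expected control responders per stratum are 56×0.04, about 2.

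**The case against.** The strongest objection is that the plan does compare like with like on frailty. Power and sample size states a null hypothesis for each stratum with its own α, power and number, Primary outcome names a frailty subgroup analysis, and the survival curves are split by arm and frailty. This stands. A reader might infer that frailty is ignored throughout the analysis, and the documents do not support that. What remains is narrower: the within-stratum tests are sized for a 20-point difference at 80% power, and the overall 10-point comparison has no stratified or adjusted estimate.

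Second, the article never calls the test unstratified. That is inferred from Table 3, the overall null hypothesis and Statistical analysis, and an analysis plan that is not shown could stratify it. The inference is sound for the method as stated, because all three places agree and none mentions a stratum or covariate.

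Third, the harm is small. This also stands. A reader might infer an invalid test, a wrong sample size or a serious loss of power, and the calculations show none of these. Chance imbalance in baseline DBI is not bias either, since the test already allows for it.

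Two further readings go too far. Baseline DBI cannot be ranked as the strongest predictor of response, because the documents give only the 0.5 floor and no distribution. Variance savings from covariance analysis of a numeric change score cannot be carried over, because the named analysis is of a proportion.

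Finally, the model has little data behind it: about 30 responders. That limits the covariates but does not rule out adjustment.

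**Conclusion.** The point holds as a modest, low-cost improvement to a stated method. The overall DBI test uses neither the randomisation strata nor baseline DBI, and it is not the same-frailty comparison described under Primary outcome. The test is valid and at most slightly conservative at the planned rates (about 4.6 to 4.8%). The expected gain is about 0 to 0.5 points of power from frailty and up to about 1.6 with baseline DBI. These sizes rest on assumed stratum rates and an assumed two-level split of baseline DBI. The direction of the baseline DBI effect follows from the entry floor and the response threshold, but its size cannot be derived from the documents. The effect could be larger for emergency department visits and unplanned admissions if those events are common and vary with frailty, but the article gives no rates for them.

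**What to change.** Name one of the following as the overall primary test of the proportion with ΔDBI ≥ 0.5:

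- a Cochran-Mantel-Haenszel test stratified by frailty, with a stratum-weighted risk difference and 95% confidence interval; or
- a logistic model with arm, frailty stratum and T1 DBI, reporting a standardised risk difference with 95% confidence interval.

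The first is less exposed to sparse data, and the second also uses baseline DBI. With about 30 responders expected, add no further covariates. Keep the plain chi-square as supportive. Stratify the emergency department and unplanned admission comparisons by frailty in the same way. State that the within-stratum comparisons at α = 0.017 are separate from this overall estimate, so that the wording under Primary outcome and the named test agree.

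The cost is analysis wording only. No extra data or participants are needed, because frailty is calculated before the home visit and medication use is recorded before the envelope is opened. The change should be dated and documented before the statistician is unblinded, which the Blinding section places after data verification and locking.

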### Data management

#### Data collection methods

All observations and results will be recorded in custom-designed Research Electronic Data Capture (REDCap https://www.project-redcap.org/) databases hosted at the University of Otago, Christchurch, New Zealand, which will allow for secure online data entry from multiple sites into a central data repository [30, 31].

A REDCap database holding details on potential study participants will contain identifying personal data separate from the database holding de-identified data for consented study participants. Access to these databases is defined in the section “Access to data.”

Data will be collected at the time of the interRAI assessment (T0), during the preparation of the intervention (T1), at least 6 months following the baseline pharmacist’s review (T2), and at the end of the study period or end of study participation for admission into aged residential care or death (T3) as detailed in Table 2.

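### All-cause mortality is given two methods that do not fit it: a Kaplan-Meier curve in which death is censored, and a competing-risk hazard ratio with no competing event

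*Protocol article*

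**What the plan says.** All places are in the protocol article.

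- **Statistical analysis**, curves: "We will present Kaplan-Meier survival curves for analysis of hospitalizations, emergency department visits, entry into aged residential care, and mortality within subgroups". The subgroups are the six arm-by-frailty combinations. Shortly afterwards: "The analyses will be controlled for age and sex, with death as a censored event".
- **Statistical analysis**, next step: "We will then conduct a competing risk analysis using cumulative incidence functions (CIF"). The one example given is that "where entry to aged residential care is the primary event of interest, death is the competing event". The cumulative incidence functions (CIFs) run to the end of the 6-month follow-up.
- **Secondary outcomes**: the outcome list includes "entry into aged residential care, all-cause mortality, and cost-utility". Deaths are matched by National Health Index (NHI) number, "added to the dataset, and analyzed using competing risk regression". **Table 3** repeats this: the measure for mortality is an HR and the analysis is competing risk regression. Neither place names a competing event for mortality.
- **Data collection methods**, and the abstract in similar words: T3 is the end of the study period or "end of study participation for admission into aged residential care or death (T3").
- **Outcomes**: for participants who enter ARC, the post-intervention medication review is still done, if need be from the facility's records. **Secondary outcomes** adds that changes in level of care within ARC will be taken from national databases.

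**The concern.** Two stated rules do not fit the outcome they are applied to.

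First, mortality is among the Kaplan-Meier endpoints, and death is then declared a censoring event for those analyses. For mortality the same occurrence cannot be both.

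Second, competing risk regression needs an event that prevents the event of interest. Nothing prevents death from any cause, so the method has no role for all-cause mortality unless some other event is put in as competing. The only other event in the document that ends participation is ARC entry, at T3. An analyst looking for a competing event could therefore choose it, and the outcome would silently become death before ARC entry.

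Mortality is a hard safety outcome in a trial that reduces medication in frail older people, and Table 3 hypothesises that it stays the same or falls. Its curve and its HR should each have one workable definition.

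**Working it through.** **Plan's own figure.** The document gives no event rate, event count or power for mortality or ARC entry. Its main design figure is 167 per arm for the DBI outcome. With 4% against 14%, two-sided α = 0.05, 90% power and unpooled variance:

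n = (1.960 + 1.282)² × (0.04×0.96 + 0.14×0.86) / 0.10² = 10.507 × 0.1588 / 0.01 = 166.9, so 167.

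It reproduces, and nothing below touches it.

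**Step 1: the mortality curve as written.** The estimator is S(t) = ∏(1 − dᵢ/nᵢ), where dᵢ counts events. If deaths are censored, every dᵢ = 0 and S(t) = 1 throughout. True 6-month mortality of 5% or 10% would both be drawn as 0%. No assumption is needed for this.

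**Step 2: the HR if ARC entry were the competing event.** Rates are assumed: control-arm 6-month death probability 5%, and ARC entry 10% or 20% (each as a net probability, with constant hazards). The intervention cuts the ARC hazard by 25% or 50% and leaves the death hazard equal in both arms, so the true all-cause HR is 1.00.

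With λd = −ln(1 − 0.05) = 0.0513 and ARC hazard λa, the cumulative incidence of death before ARC entry is

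F = λd/(λa + λd) × (1 − e^−(λa + λd)),

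and the subdistribution HR is approximated by ln(1 − F₁)/ln(1 − F₀).

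Worked case, ARC 20% and hazard halved:
- Control: λa = 0.2231, F₀ = 0.1869 × 0.2400 = 0.0449.
- Intervention: λa = 0.1116, F₁ = 0.3149 × 0.1503 = 0.0473.
- Ratio: 0.0485/0.0459 = 1.06.

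| Control ARC entry | ARC hazard cut by 25% | ARC hazard cut by 50% |
|---|---|---|
| 10% | 1.01 | 1.03 |
| 20% | 1.03 | 1.06 |

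For scale, 5% mortality in 167 per arm is 167 × 0.05 = 8.35 deaths per arm. The 95% interval for an HR is then roughly a factor of exp(1.96 × √(2/8.35)) = 2.6 either way. A shift of 1 to 6% is systematic in direction but far inside sampling error.

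**Step 3: non-fatal outcomes.** For ARC entry with death censored, compare 1−KM with the CIF (same formula, roles exchanged):

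| 1−KM for ARC | Deaths | CIF for ARC | Overstatement |
|---|---|---|---|
| 5% | 2% | 4.95% | 0.05 points |
| 10% | 5% | 9.75% | 0.25 points |
| 10% | 10% | 9.50% | 0.50 points |
| 20% | 15% | 18.5% | 1.5 points |

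The overstatement is small, and the planned CIF for ARC entry already corrects it.

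**Step 4: what T3 implies.** The T3 definition ends participation at ARC admission. On the other side are the review planned for ARC entrants, the extraction of level-of-care changes that can occur only after entry, NHI linkage that does not depend on visits, an analysis principle that includes all available data, and CIFs running to 6 months. The two sets of statements are not reconciled, and the document does not say that linked deaths after entry are dropped.

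**The case against.** The strongest reply is that the intention is clear. The censoring sentence was plausibly meant for the non-fatal outcomes, and no statistician would draw a mortality curve with no events. If linked deaths are used to 6 months and nothing competes, a Fine-Gray model reduces to an ordinary Cox model, so the competing-risk label is redundant and not biasing. The only competing-risk example in the document is the correct one, with death competing with ARC entry. This reply limits the damage, but it does not make the wording right. The sentence has no exception, and the method is assigned to mortality in both the text and Table 3.

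A reader might also infer more than the document supports:

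- **That deaths after ARC entry are lost.** If follow-up for death did stop there, about 2.5% to 25% of deaths would be missed (assumed ARC entry 5 to 20%, deaths 5 to 10%, death hazard after entry 1 to 3 times that before). T3 is a data-collection point, however, and the material in Step 4 points to continued data. This is an inconsistency to reconcile, not an established loss.
- **That the mortality HR will point the wrong way.** This needs ARC entry as the competing event, and the document never names it as such.
- **That the ARC analysis is wrong.** Table 3 assigns it competing risk regression, and CIFs with death competing follow the curves.
- **That emergency visits and admissions have contradictory analyses.** A count as the measure, a chi-squared test of proportions between arms and descriptive curves by subgroup can coexist.

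**Conclusion.** The point holds in a limited form. Two stated rules for all-cause mortality are wrong as written: censoring death in its Kaplan-Meier curve, which leaves no events, and assigning it a competing-risk HR when nothing competes with it. The first follows from the text alone. The second becomes a bias only if ARC entry is taken as the competing event. It is then modest, with an HR of about 1.01 to 1.06 in place of 1.00, given constant hazards, 5% deaths, 10 to 20% ARC entry in controls and a 25 to 50% cut in the ARC hazard. All of these rates are assumptions. The T3 wording needs reconciling because it makes that choice of competing event easier. Only secondary outcomes are involved, so this is a correction worth making before analysis and not a threat to the trial's main conclusion.

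**What to change.** 1. **Mortality** (Secondary outcomes, Table 3, Statistical analysis): analyse death from any cause by Kaplan-Meier and a Cox model with death as the event, using NHI-linked deaths to 6 months whether or not the participant has entered ARC. Replace the competing-risk entry for mortality in Table 3.
2. **Censoring sentence**: limit it to hospitalizations, emergency department visits and ARC entry. For these, take absolute risks from the CIFs already planned, with death as the competing event, and not from 1−KM.
3. **T3**: state that T3 at ARC entry does not truncate linked outcomes, so that the abstract and Data collection methods agree with Outcomes and Secondary outcomes.

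The cost is wording only. The linkage is already planned, no new data are needed and the sample size does not change. The change should be recorded before the statistician is unblinded.
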